## Staging Algorithms

### Smoking Algorithm

#### CLASSIFICATION OF THE STAGES OF CHANGE FOR SMOKING CESSATION

[figure not shown]

Smoking Stage of Change

Client ID# \_\_\_\_\_

Short Form

Date: \_\_\_\_/\_\_\_\_/\_\_\_\_

Assessment Point: \_\_\_\_\_

1. Are you currently a smoker?

- A) Yes, I currently smoke.
- B) No, I quit within the last 6 months.
- C) No, I quit more than 6 months ago.
- D) No, I have never smoked.

Smokers only:

2. In the last year, how many times have you quit smoking for at least 24 hours? \_\_\_\_\_

3. Are you seriously thinking of quitting smoking?

- A) Yes, within the next 30 days
- B) Yes, within the next 6 months
- C) No, not thinking of quitting

Smoking Stage of Change

Short Form

Scoring Sheet

1. Are you currently a smoker?

- A) Yes, I currently smoke.
- B) No, I quit within the last 6 months. (ACTION STAGE)
- C) No, I quit more than 6 months ago. (MAINTENANCE STAGE)
- D) No, I have never smoked. (NONSMOKER)

Smokers only:

2. In the last year, how many times have you quit smoking for at least 24 hours? \_\_\_\_\_

3. Are you seriously thinking of quitting smoking?

- A) Yes, within the next 30 days (PREPARATION STAGE if they have one 24-hour quit attempt in the past year; if there was no quit attempt in the past year, then CONTEMPLATION STAGE)
- B) Yes, within the next 6 months (CONTEMPLATION)
- C) No, not thinking of quitting (PRECONTEMPLATION)

## Readiness Ruler

[figure not shown]

**Tobacco is not a problem for me.**  
**I don't want to quit.**  
**Trying to quit would be a waste of my time.**

**I know that quitting would be good for my health.**  
**I am interested in advice about quitting.**

**I am ready to quit using tobacco.**  
**I would like help to quit using tobacco.**

MARYLAND RESOURCE CENTER  
FOR QUITTING USE & INITIATION OF TOBACCO

Maryland's  
**1-800** [figure not shown] **QUIT NOW**  
[SmokingStopsHere.com](http://SmokingStopsHere.com)

## Appendix C: Tools for Varenicline Use

### Appendix C1: Varenicline Indications and Uses

#### INDICATIONS AND USAGE

CHANTIX is a nicotinic receptor partial agonist indicated for use as an aid to smoking cessation treatment. ([1](#) and [2.1](#))

#### DOSAGE AND ADMINISTRATION

Begin CHANTIX dosing one week before the date set by the patient to stop smoking. Alternatively, the patient can begin CHANTIX dosing and then quit smoking between days 8 and 35 of treatment. ([2.1](#))

Starting Week: 0.5 mg once daily on days 1–3 and 0.5 mg twice daily on days 4–7. ([2.1](#))

Continuing Weeks: 1 mg twice daily for a total of 12 weeks. ([2.1](#))

An additional 12 weeks of treatment is recommended for successful quitters to increase likelihood of long-term abstinence. ([2.1](#))

Consider a gradual approach to quitting smoking with CHANTIX for patients who are sure that they are not able or willing to quit abruptly. Patients should begin CHANTIX dosing and reduce smoking by 50% from baseline within the first four weeks, by an additional 50% in the next four weeks, and continue reducing with the goal of reaching complete abstinence by 12 weeks. Continue treatment for an additional 12 weeks, for a total of 24 weeks. ([2.1](#))

Severe Renal Impairment (estimated creatinine clearance less than 30 mL/min): Begin with 0.5 mg once daily and titrate to 0.5 mg twice daily. For patients with end-stage renal disease undergoing hemodialysis, a maximum of 0.5 mg daily may be given if tolerated. ([2.2](#))

Consider dose reduction for patients who cannot tolerate adverse effects. ([2.1](#))

Another attempt at treatment is recommended for those who fail to stop smoking or relapse when factors contributing to the failed attempt have been addressed. ([2.1](#))

Provide patients with appropriate educational materials and counseling to support the quit attempt. ([2.1](#))

#### DOSAGE FORMS AND STRENGTHS

Tablets: 0.5 mg and 1 mg ([3](#))

#### CONTRAINDICATIONS

History of serious hypersensitivity or skin reactions to CHANTIX. ([4](#))

#### WARNINGS AND PRECAUTIONS

**Neuropsychiatric Adverse Events:** Postmarketing reports of serious or clinically significant neuropsychiatric adverse events have included changes in mood (including depression and mania), psychosis, hallucinations, paranoia, delusions, homicidal ideation, aggression, hostility, agitation, anxiety, and panic, as well as suicidal ideation, suicide attempt, and completed suicide. Observe patients attempting to quit smoking with CHANTIX for the occurrence of such symptoms and instruct them to discontinue CHANTIX and contact a healthcare provider if they experience such adverse events. ([5.1](#))

**Seizures:** New or worsening seizures have been observed in patients taking CHANTIX. CHANTIX should be used cautiously in patients with a history of seizures or other factors that can lower the seizure threshold. ([5.2](#))

**Interaction with Alcohol:** Increased effects of alcohol have been reported. Instruct patients to reduce the amount of alcohol they consume until they know whether CHANTIX affects them. ([5.3](#))

**Accidental Injury:** Accidental injuries (e.g., traffic accidents) have been reported. Instruct patients to use caution driving or operating machinery until they know how CHANTIX may affect them. ([5.4](#))

Cardiovascular Events: Patients with underlying cardiovascular (CV) disease may be at increased risk of CV events; however, these concerns must be balanced with the health benefits of smoking cessation. Instruct patients to notify their healthcare providers of new or worsening CV symptoms and to seek immediate medical attention if they experience signs and symptoms of myocardial infarction (MI) or stroke. ([5.5](#) and [6.1](#))

Somnambulism: Cases of somnambulism have been reported in patients taking CHANTIX. Some cases described harmful behavior to self, others, or property. Instruct patients to discontinue CHANTIX and notify their healthcare provider if they experience somnambulism. ([5.6](#) and [6.2](#))

Angioedema and Hypersensitivity Reactions: Such reactions, including angioedema, infrequently life-threatening, have been reported. Instruct patients to discontinue CHANTIX and immediately seek medical care if symptoms occur. ([5.7](#) and [6.2](#))

Serious Skin Reactions: Rare, potentially life-threatening skin reactions have been reported. Instruct patients to discontinue CHANTIX and contact a healthcare provider immediately at first appearance of skin rash with mucosal lesions. ([5.8](#) and [6.2](#))

Nausea: Nausea is the most common adverse reaction (up to 30% incidence rate). Dose reduction may be helpful. ([5.9](#))

## **ADVERSE REACTIONS**

Most common adverse reactions (>5% and twice the rate seen in placebo-treated patients) were nausea, abnormal (e.g., vivid, unusual, or strange) dreams, constipation, flatulence, and vomiting. ([6](#))

**To report SUSPECTED ADVERSE REACTIONS, contact Pfizer Inc. at [name] or FDA at [name] or [www.fda.gov/medwatch](http://www.fda.gov/medwatch).**

## **DRUG INTERACTIONS**

Other Smoking Cessation Therapies: Safety and efficacy in combination with other smoking cessation therapies has not been established. Coadministration of varenicline and transdermal nicotine resulted in a high rate of discontinuation due to adverse events. ([7.1](#))

Effect of Smoking Cessation on Other Drugs: Pharmacokinetics or pharmacodynamics of certain drugs (e.g., theophylline, warfarin, insulin) may be altered, necessitating dose adjustment. ([7.2](#))

## Appendix C2: Common Terminology Criteria for adverse Events and Common Toxicity Criteria

(See accompanying PDF)

### Appendix C3: Exclusion Criteria for Varenicline Use

| Criteria                                                                                                                                 | Mode of Detection                                   |
|------------------------------------------------------------------------------------------------------------------------------------------|-----------------------------------------------------|
| Previous Allergic Reaction or hypersensitivity to Varenicline                                                                            | Participant report ever in lifetime                 |
| Pregnant, nursing, or becoming pregnant during the study                                                                                 | Pregnancy Test                                      |
| Current use of any medication that could interfere with the protocol (such as Bupropion)                                                 | Patient history and chart review                    |
| Moderate to severe renal impairment                                                                                                      | Patient history and chart review                    |
| Unstable cardiovascular disease (myocardial infarction in the past year, uncontrolled arrhythmia, uncontrolled congestive heart failure) | Clinician assessment and chart review               |
| The study clinician feels the individual is not medically stable enough to participate in the study                                      | Past medical history and/ or current medical status |
|                                                                                                                                          |                                                     |

### BSMART Medication Adherence Form

|                           |                        |
|---------------------------|------------------------|
| Researcher ID:     | Participant ID: |
| District:          | Facility:       |
| Date: (dd/mm/yyyy) |                        |

(Completed only at Week 1, 2, 3, 4, 8, and 12)

|                                 |                                 |                                 |                                 |                                 |                                  |
|---------------------------------|---------------------------------|---------------------------------|---------------------------------|---------------------------------|----------------------------------|
| Week:                    |                                 |                                 |                                 |                                 |                                  |
|  Week 1 |  Week 2 |  Week 3 |  Week 4 |  Week 8 |  Week 12 |

**How many days last week did you take at least 1 of your study pills?**

\_\_\_\_\_

(Completed only at week 2, 3, 4, 8, and 12)

|                                 |                                 |                                 |                                 |                                  |
|---------------------------------|---------------------------------|---------------------------------|---------------------------------|----------------------------------|
| Week:                    |                                 |                                 |                                 |                                  |
|  Week 2 |  Week 3 |  Week 4 |  Week 8 |  Week 12 |

**How many days last week did you take at least 2 of your study pills?**

\_\_\_\_\_

## Appendix C5: BSMART Side-effects Checklist

### BSMART Side Effect Checklist

|                            |                        |
|----------------------------|------------------------|
| Researcher ID:      | Participant ID: |
| District:           | Facility:       |
| Date: (dd/mon/yyyy) |                        |

|                                        |                                        |                                        |                                        |                                        |                                         |
|----------------------------------------|----------------------------------------|----------------------------------------|----------------------------------------|----------------------------------------|-----------------------------------------|
| Week Number:                    |                                        |                                        |                                        |                                        |                                         |
|  Week 1 |  Week 2 |  Week 3 |  Week 4 |  Week 8 |  Week 12 |

Ask the participant if he/she experienced these side effects in the last week. If participant endorses a side effect, then ask if it was mild, moderate or severe. If participant endorses a side effect, also ask how often it happened and if they took any medications for it or called a doctor. Make any notes at the back of this form. Use the following format: "Did you experience nausea in the last week?" If yes, continue with: "Would you say the nausea was mild, moderate or severe? How often did you experience nausea in the last week? Did you take any medications or call a doctor for your nausea in the last week?"

| Side Effect                    | None
(0)              | Mild
(1)              | Moderate
(2)          | Severe
(3)            | Not
Rated
(4)      | Missing
(99)          | Related to Medication:
A = None; B = Remote;
C = Possible; D = Probable;
E = Missing                                          |
|--------------------------------|--------------------------|--------------------------|--------------------------|--------------------------|--------------------------|--------------------------|----------------------------------------------------------------------------------------------------------------------------------------|
| 1. Nausea                      |  A  B  C  D  E |
| 2. Vomiting                    |  A  B  C  D  E |
| 3. Constipation                |  A  B  C  D  E |
| 4. Dizziness                   |  A  B  C  D  E |
| 5. Disturbance in attention    |  A  B  C  D  E |
| 6. Anorexia (loss of appetite) |  A  B  C  D  E |
| 7. Increased appetite          |  A  B  C  D  E |
| 8. Weight loss                 |  A  B  C  D  E |

|                                            |                          |                          |                          |                          |                          |                          |                                                                                                                                        |
|--------------------------------------------|--------------------------|--------------------------|--------------------------|--------------------------|--------------------------|--------------------------|----------------------------------------------------------------------------------------------------------------------------------------|
| 9. Weight increase                         |  A  B  C  D  E |
| 10. Gastroesophageal reflux                |  A  B  C  D  E |
| 11. Dyspepsia (indigestion)                |  A  B  C  D  E |
| 12. Insomnia                               |  A  B  C  D  E |
| 13. Abnormal dreams                        |  A  B  C  D  E |
| 14. Sleep disorder                         |  A  B  C  D  E |
| 15. Nightmares                             |  A  B  C  D  E |
| 16. Abdominal pain                         |  A  B  C  D  E |
| 17. Chest pain                             |  A  B  C  D  E |
| 18. Back pain                              |  A  B  C  D  E |
| 19. Myalgia (muscle pain)                  |  A  B  C  D  E |
| 20. Arthralgia (joint pain)                |  A  B  C  D  E |
| 21. Stiffness                              |  A  B  C  D  E |
| 22. Tremor                                 |  A  B  C  D  E |
| 23. Restlessness                           |  A  B  C  D  E |
| 24. Headache                               |  A  B  C  D  E |
| 25. Fever                                  |  A  B  C  D  E |
| 26. Sore throat                            |  A  B  C  D  E |
| 27. Dry mouth                              |  A  B  C  D  E |
| 28. Hypersalivation                        |  A  B  C  D  E |
| 29. Mucousal ulceration                    |  A  B  C  D  E |
| 30. Toothache                              |  A  B  C  D  E |
| 31. Dysgeusia (metallic taste)             |  A  B  C  D  E |
| 32. Respiratory Disorder                   |  A  B  C  D  E |
| 33. Dyspnea (labored breathing)            |  A  B  C  D  E |
| 34. Rhinorrhea (nasal mucous)              |  A  B  C  D  E |
| 35. Malaise
(fatigue/asthenia/lethargy) |  A  B  C  D  E |
| 36. Epidermal/dermal pruritus
(rash)    |  A  B  C  D  E |
| 37. Urticaria (hives, itching)             |  A  B  C  D  E |

|                                    |                          |                          |                          |                          |                          |                          |                                                                                                                                        |
|------------------------------------|--------------------------|--------------------------|--------------------------|--------------------------|--------------------------|--------------------------|----------------------------------------------------------------------------------------------------------------------------------------|
| 38. Bruising easily                |  A  B  C  D  E |
| 39. Tinnitus (ringing in the ears) |  A  B  C  D  E |
| 40. Liver abnormalities            |  A  B  C  D  E |
| 41. Other _____                    |  A  B  C  D  E |
| 42. Other _____                    |  A  B  C  D  E |
| 43. Other _____                    |  A  B  C  D  E |
| 44. Other _____                    |  A  B  C  D  E |
| 45. Additional Comments:           |                          |                          |                          |                          |                          |                          |                                                                                                                                        |

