### Provision of varenicline

Participants referred for treatment with varenicline will be taught the correct use of varenicline by the nurse prescriber/ dispenser (NPD) at the site where the participant receives care. Participants will initiate medication treatment with varenicline for smoking cessation with a quit date scheduled for day 8 following the first study dose of the medication. Participants will meet with the NPD at baseline who will evaluate them, provide medical clearance and sign off on prescription orders if they meet the requirements for varenicline use (See Appendix IX). Varenicline will be prescribed in accordance with package labeling and provided to participants by the nurse prescriber/ dispenser. Participants will receive a weekly supply of medication for the first four weeks to ensure proper dosing and monitoring for adverse events. For the subsequent eight weeks, participants will return every 4 weeks to receive the next month’s supply of medication. Dosage adjustments will be permitted in an effort to control adverse effects throughout the trial. This will allow us to balance internal validity with good clinical practice.

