### Monitoring for adverse events

Adverse event monitoring will be provided by the nurse prescriber/dispenser every time a participant picks up their medication.

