## Retention

We will leverage the current approach which utilizes lay health workers and expert clients to ensure retention in the study and include additional strategies such as information leaflets about the importance of retention, appointment cards, motivational text messages, and phone calls (and home visits) to remind participants of appointments. All participants who miss study visits will be contacted.

| Table 3: Participant Timeline - Intervention Phase |                    |          |     |     |     |     |     |     |     |     |      |      |
|----------------------------------------------------|--------------------|----------|-----|-----|-----|-----|-----|-----|-----|-----|------|------|
|                                                    | Responsible person | Baseline | W 1 | W 2 | W 3 | W 4 | W 5 | W 6 | W 7 | W 8 | W 12 | W 24 |
| Screening of participants                          | LHW case manager   | X        |     |     |     |     |     |     |     |     |      |      |
| Informed Consent                                   | Research Assistant | X        |     |     |     |     |     |     |     |     |      |      |
| Enrollment in BSMART study                         | Research Assistant | X        |     |     |     |     |     |     |     |     |      |      |
| Intake Smoking Questionnaire                       | Research Assistant | X        |     |     |     |     |     |     |     |     |      |      |
| Follow-up smoking questionnaire                    | Research Assistant |          |     |     |     | X   |     |     |     |     | X    | X    |
| Stages of change                                   | Research Assistant | X        |     |     |     | X   |     |     |     |     | X    | X    |
| SBIRT Intervention                                 | LHW case manager   | X        |     |     |     |     |     |     |     |     |      |      |
| Breath CO                                          | Research Assistant | X        |     |     |     |     |     |     |     |     | X    | X    |
| Adherence to varenicline                           | Nurse prescribers  |          | X   | X   | X   | X   |     |     |     | X   |      |      |
| Adverse events monitoring                          | Nurse prescribers  |          | X   | X   | X   | X   | X   | X   | X   | X   |      |      |

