### Estimating process and outcome measures

All procedures will be conducted according to the local standards of routine clinical care. The following measures will be utilized:

1. **Baseline Demographic Information:** Baseline information will be abstracted from the HIV medical records and collected using a questionnaire. Baseline information will include demographics, medical history, laboratory values measured as part of HIV care (e.g. viral load, CD4), antiretroviral (ARV) history and ART treatment regimen (for current patients), and ART treatment start date. Because of high viral load suppression and high retention rate in this population, we will not be analyzing HIV treatment variables as mediators or outcomes.
2. **5”A”s (SBIRT) checklist:** This checklist will be completed by the LHW case managers and will serve to document the delivery of the intervention. A 10% random sample of the completed 5”A”s checklist will be reviewed by [name] during the time that a site is engaged in the intervention to ensure fidelity to the study intervention.
3. **Intake Smoking History Questionnaire** will measure length of smoking, use of other tobacco products, quit attempts, length of longest quit attempt, and smokers in the immediate living environment.
4. **Follow-up Smoking Use Questionnaire** will measure 7-day and 30-day point prevalence abstinence, number of cigarettes smoked (if not abstinent), stage of change and readiness to quit (if not abstinent), length of longest period of abstinence since last evaluation, use of varenicline, side effects, reasons for using or not using varenicline, and length of varenicline use.

5. **Stages of Change Algorithm** and **the Readiness Ruler**, will be used at baseline and follow-up to determine each individual's stage of change for quitting tobacco.
6. **Smoking Abstinence**: Abstinence will be based on self-reported 7-day point prevalence abstinence confirmed by expired CO < 6 ppm. Abstinence criteria must be met in participant Month 6 or at an earlier study week and maintained through participant Month 6 to be considered a responder. We will use coVita CO Smokerlyzer, a single-breath point-of-care tool designed specifically for use in smoking cessation programs and clinics.

For those who agree to be treated with varenicline:

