7. **Adherence to Medication**: Pill and counseling adherence will be assessed at Weeks 0, 1, 2, 4, 8, and 12. Pill adherence will be tracked by the following question at each medication visit: How many days in the last week did you take at least one of your study pills. Pill adherence will be defined by participant self-report of taking six or seven pills at week eight which coincides with their last receipt of varenicline.
8. **Adverse Event Monitoring** (Baseline, weekly for 4 weeks then every 4 weeks until week 12): Adverse events will be monitored at each study contact and classified and graded using the Common Terminology Criteria for Adverse Events and Common Toxicity Criteria provided by the National Cancer Institute. Our protocol for responding to Serious Adverse Events is summarized in the Human Subjects section.  
  
The 5 "A"s (SBIRT) Checklist and the Intake Smoking History Questionnaire will be administered at baseline for PLWH newly enrolling to HIV treatment and those currently on HIV treatment. A Follow-up Smoking Use Algorithm will be administered at baseline and at 4-, 12-, and 24-weeks of follow-up. The CO measurement will be obtained at baseline, 12 and 24 weeks of patient follow-up using coVita CO Smokerlyzer .

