We will closely monitor for depressive and other neuropsychiatric symptoms and have a careful plan in place for any exacerbation of symptoms or suicidality. All participants will be thoroughly informed of the various side-effects of varenicline, which they might experience and will be appropriately cautioned concerning their activities in the hours after administration. Since participation is voluntary, participants can withdraw at any time if they find the behavioral procedures or drug effects undesirable. Each time a participant receives their medication, the prescribing clinicians will assess for adverse side effects using a standardized questionnaire. If a participant reports depressed mood or suicidal ideation, the participant will receive an immediate evaluation by a qualified clinician to ensure participant safety and proper provision of treatment. Treatment with varenicline will be stopped for any participant experiencing these types of adverse events. Further participation in the study will be decided upon with input from the treating clinician, the research team and the participant.

We are aware that in September 2021 Pfizer voluntarily recalled varenicline (marketed under the brand name Chantix) due to concern that the medication may contain levels of N-nitroso-varenicline above the FDA limit (37ng per day). It is important to note that other makers of varenicline (i.e., Apotex) did not have this problem with their manufacturing of varenicline and remain FDA approved. <https://www.fda.gov/drugs/drug-safety-and-availability/fda-updates-and-press-announcements-nitrosaminevarenicline-chantix>

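### The nurse side-effect checklist does not ask about 6 of the 12 varenicline weeks, and Table 3 omits the week 12 adverse event check that the text and the checklist plan

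*Protocol*

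**What the plan says.** **Checklist.** Appendix C5 has boxes for weeks 1, 2, 3, 4, 8 and 12. The instruction to the nurse is "Ask the participant if he/she experienced these side effects in the last week", and the scripted questions use the same one-week window. There is no alternative wording for weeks 8 and 12.

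**Text.** In the section on estimating process and outcome measures, the adverse event monitoring item sets the schedule as "Baseline, weekly for 4 weeks then every 4 weeks until week 12". It also calls for monitoring at each study contact, without a recall window.

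**Table 3.** The row "Adverse events monitoring" is marked at every week from W1 to W8 and is blank at Baseline, W12 and W24.

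**Medication visits.** Supply is weekly for four weeks. Then: "For the subsequent eight weeks, participants will return every 4 weeks". The adherence item measures adherence "at week eight which coincides with their last receipt of varenicline". The prescription form (Appendix C7) continues dosing through week 12. Nurse monitoring takes place "every time a participant picks up their medication", and the section on potential risks adds: "Each time a participant receives their medication, the prescribing clinicians will assess for adverse side effects using a standardized questionnaire".

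**The concern.** A one-week question fits a weekly check because the window and the interval match. From week 4 the interval on this form becomes four weeks and the window does not change. A symptom that starts and resolves in week 6, for example, is asked about at neither week 4 nor week 8. The checklist therefore prompts for all four weeks of month 1 but for only one week in four in months 2 and 3. Any count of participants who ever had a given symptom would be less complete for the later months.

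The Table 3 discrepancy matters in a different way. A visit table is what site staff are likely to work from. Read alone, it ends nurse monitoring at the visit where the last four weeks of drug are handed out. It also asks for checks at W5 to W7, where no medication visit is scheduled, no other procedure is marked and the checklist has no box.

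**Working it through.** The plan states no figure to reproduce, so the check is a count of weeks.

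**Inputs**
- Treatment weeks: 1 to 12 (Appendices C1 and C7).
- Look-back at each check: 7 days (Appendix C5).
- Check weeks: 1, 2, 3, 4, 8 and 12 in Appendix C5 and in the adverse event monitoring item; W1 to W8 in Table 3. A baseline check covers no treatment week.

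**Rule.** With a 7-day look-back, a check at week *w* asks about week *w* only. Weeks not asked about = {1, ..., 12} minus the set of check weeks.

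| Schedule | Weeks asked about | Weeks not asked about | Count |
|---|---|---|---|
| Appendix C5 and the monitoring item | 1, 2, 3, 4, 8, 12 | 5, 6, 7, 9, 10, 11 | 12 - 6 = 6 of 12 |
| Table 3 | 1 to 8 | 9, 10, 11, 12 | 12 - 8 = 4 of 12 |
| Both combined | 1 to 8, 12 | 9, 10, 11 | 12 - 9 = 3 of 12 |
| Appendix C5 with an interval question at weeks 8 and 12 | 1 to 12 | none | 0 of 12 |

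On the form as printed, 6 x 7 = 42 of 84 treatment days are asked about. With the interval question, week 8 reaches back over weeks 5-8 and week 12 over weeks 9-12, which gives 84 of 84. The combined row assumes that the form is used at W5 to W7 although it has no boxes for them.

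**Cell-by-cell comparison of Table 3 with the text**
- W1 to W4 and W8: agree.
- W5, W6, W7: marked in Table 3; absent from the text and from Appendix C5.
- W12: in the text and in Appendix C5; blank in Table 3.
- Baseline: in the text only. This is minor, because it precedes the first dose.

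The Table 3 row appears to have been read correctly from the PDF: the adherence row of the same table falls at W1 to W4 and W8, which fits the dispensing visits.

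**The case against.** **A 7-day window is a legitimate choice.** It gives comparable per-visit data and more accurate recall than a four-week question. This stands as a reason to keep the question. It does not justify asking nothing about the other three weeks, and the protocol nowhere presents the window as deliberate sampling.

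**Other routes collect these events.** This stands in large part. Adverse events are to be monitored at each study contact and collected at each follow-up visit, and study staff review participant records for missed events. Appendix C5 has four open lines, a comments line and room for notes. Serious events, and reports of depressed mood or suicidal ideation, have their own procedures. The protocol also assigns "use of varenicline, side effects, reasons for using or not using varenicline" to the follow-up questionnaire, which is given at week 12. In the printed form (Appendix B4), however, the symptom list concerns problems while trying to quit and is skipped without a quit of at least 24 hours. Together these routes narrow the gap without closing it, because none is a scripted prompt to every treated participant for the missing weeks.

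**Stronger readings that the documents do not support**
- *Events in the six weeks cannot be recorded.* They can, by the routes above. The count is of weeks not asked about, not of events lost.
- *The pick-up rule is a further rival schedule that ends monitoring at week 8.* The protocol says that checks happen at each pick-up. It does not say that they happen only then, so the rule is compatible with a week 12 check.
- *The W5 to W7 marks are simply errors.* Table 3 has those columns for adverse event checks alone, so they may be intended interim contacts. Deleting them outright could remove three planned safety checks.

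**Conclusion.** The point holds in two limited parts. First, the checklist does not prompt for weeks 5-7 and 9-11, 6 of 12 treatment weeks. Second, Table 3 conflicts with the text and with Appendix C5 at W5 to W7 and at W12. The W12 conflict has the practical consequence: a site following Table 3 makes no nurse check after week 8, while the last supply runs to week 12.

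The likely loss is confined to transient, non-serious symptoms that begin and end between four-weekly checks and are not volunteered. Symptoms still present in the week before a check are captured. The primary endpoint is unaffected, and adverse events are not among the listed primary or secondary outcomes. Severity is minor.

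This rests on three assumptions: that nurses use the questions as scripted, that visits fall on schedule, and that the other reporting routes work as described. The number of symptoms missed cannot be estimated from the protocol.

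**What to change.** 1. In Appendix C5, at weeks 8 and 12, keep the 7-day question and add one on symptoms *since your last adverse event check*.
2. Mark W12 in the adverse event row of Table 3.
3. Settle W5 to W7. Either state that they are interim contacts and give them boxes on Appendix C5, or remove them, but only once the interval question at week 8 is in place.
4. While editing, align Baseline between the text, Table 3 and Appendix C5.

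**Cost.** A wording change to the form and its electronic version, one table row and a training note. The W12 change adds no visit: week 12 is already a study visit in Table 3, and the text and checklist already plan the check there. Interviews at two visits become slightly longer, and four-week recall is less precise than one-week recall, which is why the 7-day question should stay. If W5 to W7 are removed, three marked checks are given up and the week 8 interval question has to cover those weeks.
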